# Neoadjuvant FOLFOXIRI prior to chemoradiotherapy for high-risk (“ugly”) locally advanced rectal cancer: study protocol of a single-arm, multicentre, open-label, phase II trial (MEND-IT)

**DOI:** 10.1186/s12885-022-09947-w

**Published:** 2022-09-06

**Keywords:** Locally advanced rectal cancer, Induction chemotherapy, Neoadjuvant chemotherapy, Neoadjuvant treatment, Pathological complete response, Clinical complete response, Complete response

## Abstract

**Background:**

The presence of mesorectal fascia (MRF) invasion, grade 4 extramural venous invasion (EMVI), tumour deposits (TD) or extensive or bilateral extramesorectal (lateral) lymph nodes (LLN) on MRI has been suggested to identify patients with indisputable, extensive locally advanced rectal cancer (LARC), at high risk of treatment failure. The aim of this study is to evaluate whether or not intensified chemotherapy prior to neoadjuvant chemoradiotherapy improves the complete response (CR) rate in these patients.

**Methods:**

This multicentre, single-arm, open-label, phase II trial will include 128 patients with non-metastatic high-risk LARC (hr-LARC), fit for triplet chemotherapy. To ensure a study population with indisputable, unfavourable prognostic characteristics, hr-LARC is defined as LARC with on baseline MRI at least one of the following characteristics; MRF invasion, EMVI grade 4, enlarged bilateral or extensive LLN at high risk of an incomplete resection, or TD. Exclusion criteria are the presence of a homozygous DPD deficiency, distant metastases, any chemotherapy within the past 6 months, previous radiotherapy within the pelvic area precluding standard chemoradiotherapy, and any contraindication for the planned treatment. All patients will be planned for six two-weekly cycles of FOLFOXIRI (5-fluorouracil, leucovorin, oxaliplatin and irinotecan) prior to chemoradiotherapy (25 × 2 Gy or 28 × 1.8 Gy with concomitant capecitabine). A resection will be performed following radiological confirmation of resectable disease after the completion of chemoradiotherapy. A watch and wait strategy is allowed in case of a clinical complete response. The primary endpoint is the CR rate, described as a pathological CR or a sustained clinical CR one year after chemoradiotherapy. The main secondary objectives are long-term oncological outcomes, radiological and pathological response, the number of resections with clear margins, treatment-related toxicity, perioperative complications, health-related costs, and quality of life.

**Discussion:**

This trial protocol describes the MEND-IT study. The MEND-IT study aims to evaluate the CR rate after intensified chemotherapy prior to concomitant chemoradiotherapy in a homogeneous group of patients with locally advanced rectal cancer and indisputably unfavourable characteristics, defined as hr-LARC, in order to improve their prognosis.

**Trial registration:**

Clinicaltrials.gov: NCT04838496, registered on 02–04-2021 Netherlands Trial Register: NL9790.

**Protocol version:**

Version 3 dd 11–4-2022.

## Background

Locally advanced rectal cancer (LARC) is often defined as a clinically staged (c) T3 tumour within 1 mm from the mesorectal fascia (MRF), a cT4 tumour, cN2 disease, or rectal cancer in the presence of extramesorectal lymph nodes [1–3]. Standard treatment consists of neoadjuvant chemoradiotherapy prior to surgery, i.e. a total mesorectal excision [1, 4, 5]. However, despite optimal treatment, LARC is associated with local recurrence and distant metastasis rates ranging between 5–10% and 25–40%, respectively [5–12]. This has resulted in an ongoing search for better treatment regimens in patients at high risk of treatment failure.

The main aim of neoadjuvant treatment is to obtain downstaging to facilitate a resection with clear resection margins (R0) [5, 6, 13]. An R0 resection is an important prognostic factor for disease-free survival, particularly due to an improved local recurrence-free survival [5, 8, 14, 15]. In addition, the introduction of neoadjuvant treatment regimens has translated into new treatment strategies, focusing on organ preservation [16–19]. Previous studies reported a pathological complete response (pCR) rate, i.e. the absence of malignant cells on pathological examination after surgery, in over 15% of the patients treated with neoadjuvant chemoradiotherapy [16, 20–22]. Improved long-term outcomes, probably related to a favourable tumour biology, have been suggested in patients with a pCR [22, 23]. Subsequently, an organ preservation strategy with active surveillance, referred to as a watch and wait (W&W) strategy, has been introduced to prevent unnecessary surgical morbidity and mortality without comprising (disease-free) survival [16–19].

Nonetheless, substantial improvements in distant metastasis rates and overall survival for patients with LARC are lagging behind [3]. The administration of adjuvant chemotherapy to reduce distant metastasis rates and improve overall survival in rectal cancer is controversial [3, 24, 25]. As an alternative, the addition of neoadjuvant chemotherapy to the current treatment regimen has been suggested [26–29]. A matched case–control study observed an improved complete response (CR) rate of 28% compared to 9% (p = 0.013) with the addition of doublet chemotherapy to neoadjuvant treatment in patients with unfavourable LARC, defined as any cT4 rectal cancer, or cT2/3 rectal cancer with extramural venous invasion (EMVI), and/or tumour deposits, and/or cN2 disease on magnetic resonance imaging (MRI) [30]. These results on CR are in line with those of three recently published, phase III randomised controlled trials in LARC [28, 31, 32]. In the PRODIGE 23 trial patients with cT3 rectal cancer eligible for chemoradiotherapy and cT4 rectal cancer were randomly assigned to either chemoradiotherapy alone or neoadjuvant FOLFIRINOX (fluorouracil, irinotecan, leucovorin, oxaliplatin) followed by chemoradiotherapy prior to surgery [32]. The RAPIDO trial included patients with an involved MRF (the primary tumour or a lymph node on a distance of ≤ 1 mm from the MRF), cT4 disease, extramural vascular invasion, cN2 disease, or enlarged lateral lymph nodes [33]. These patients were treated with either chemoradiotherapy alone or short-course radiotherapy followed by neoadjuvant doublet chemotherapy (a fluoropyrimidine in combination with oxaliplatin; CAPOX/FOLFOX) [33]. Despite the improvement in CR rate and 3-year disease-free survival / disease-related treatment failure in patients treated with neoadjuvant chemotherapy, no substantial improvements in overall survival were reported in either trial [32, 33]. Moreover, in the RAPIDO trial, the locoregional failure rate at 5 years was higher in the experimental group compared to the standard of care group (10% versus 7%, *p* = 0.038), whereas the significant difference in distant metastasis rate (23% versus 31%, *p* = 0.011) remained favourable for the experimental group [34]. In the STELLAR trial, patients with cT3-4 and/or node-positive disease were randomised between either neoadjuvant chemoradiotherapy or short-course radiotherapy followed by doublet chemotherapy [28]. A non-inferior 3-year disease-free survival was observed in the experimental arm, and preliminary results suggested a benefit in 3-year overall survival in this group [28]. However, a longer follow-up is awaited to draw definite conclusions, considering the disappearance of an overall survival benefit in the Polish II trial after a 8 year follow-up period [35]. Apart from these survival outcomes, an increase in preoperative ≥ grade 3 adverse events was reported in the experimental arms [28, 32, 33]. Nevertheless, the administration of both doublet and triplet chemotherapy did not result in significantly less patients proceeding to surgery compared to the standard treatment arms [32, 33].

Hence, neoadjuvant chemotherapy in combination with (chemo)radiotherapy may improve short- and long-term outcomes in LARC. However, the absence of a substantial improvement in overall survival, the increased risk of treatment-related toxicity, possibly resulting in treatment delays, the differences in patient selection and treatment regimens among different studies, and the underrepresentation of patients with the prognostic most unfavourable rectal tumours hamper the clinical implementation of neoadjuvant chemotherapy in rectal cancer [29, 31, 36–40]. Moreover, overrepresentation of patients who do not need additional systemic treatment for cure, may also dilute positive oncological results. As a consequence, it has been hypothesised that total neoadjuvant treatment, consisting of both neoadjuvant chemotherapy and chemoradiotherapy, should be preserved for a select group of patients facing the worst prognosis [31].

Since the start of the RAPIDO trial in 2011, imaging-based staging has been further refined [33]. High-risk imaging-based features were more routinely described and studied, which resulted in the recognition of clinically important, unfavourable characteristics on MRI [33, 41–43]. An involved MRF, defined as a distance of ≤ 1 mm to the MRF, has already been recognized as an important, unfavourable prognostic feature for several years [44, 45]. In addition, the identification of EMVI, tumour deposits, or enlarged extramesorectal (lateral) lymph nodes (LLN) with a short-axis of at least 7 mm on baseline MRI has been suggested to identify patients with the most ‘ugly’ LARC, at high risk of failure on current treatment regimens [33, 42, 46–51]. A significantly decreased disease-free and overall survival rate has been described for patients with EMVI-positive rectal cancer, with 5-year distant metastasis rates up to 45.2%, compared to EMVI-negative rectal cancer (25.7%) [12]. In addition, the presence of tumour deposits on baseline MRI has been identified as an independent prognostic factor, indicating a poor survival [42, 52]. Lastly, a lateral local recurrence rate of up to 19.5% has been described in patients with lateral lymph nodes, located in the iliac or obturator compartment, with a short-axis of at least 7 mm on baseline MRI despite treatment with chemoradiotherapy prior to a total mesorectal excision [48].

Hence, these imaging-based, high-risk features may be used to identify patients with LARC facing the worst prognosis, at high risk of failing on current treatment regimens. Nevertheless, it has been described that the recognition of imaging-based MRF involvement might be overestimated [45, 51, 53, 54]. In addition, the presence of EMVI is evaluated based on a scoring system, classifying both grade 3 and 4, in contrast to grade 0–2, as EMVI-positive [55]. Grade 3 might comprise more subtle, possibly debatable, EMVI, whereas grade 4 describes evident EMVI with obvious vessel abnormalities [55]. Therefore, we hypothesise that the presence of evident MRF invasion, EMVI grade 4, extensive or bilateral enlarged lateral lymph nodes, or tumour deposits, we refer to as MEND criteria, will correctly identify a homogeneous group of patients with high-risk (hr-) LARC, facing the worst prognosis.

This select group of patients fulfilling the MEND criteria might benefit from an intensified treatment regimen. However, these patients were underrepresent in previous trials [28, 32, 33]. The addition of intensified induction chemotherapy (IT), consisting of FOLFOXIRI (5-fluorouracil, irinotecan, leucovorin, oxaliplatin) has been suggested. This triplet chemotherapy regimen has been associated with a significantly improved tumour response of over 10%, progression-free survival and overall survival compared to a doublet chemotherapy regimen in patients diagnosed with metastatic colorectal cancer [56–58]. The PRODIGE 23 trial confirmed that the majority of the patients in the experimental arm was treated with chemoradiotherapy after neoadjuvant, triplet chemotherapy (95%), compared to 99% in the standard of care arm (*p* = 0.019) [32]. Moreover, the addition of both doublet and triplet chemotherapy to neoadjuvant (chemo)radiotherapy did not result in less patients proceeding to surgery compared to standard treatment [32, 33].

In conclusion, personalised medicine in rectal cancer is warranted to improve surgical and oncological outcomes and to prevent both over- and undertreatment. The primary aim of this single-arm, phase II study is to evaluate whether neoadjuvant chemotherapy with FOLFOXIRI prior to chemoradiotherapy provides an increased CR rate in a homogeneous group of patients with hr-LARC, fulfilling the MEND criteria, compared to current literature.

## Methods/design

### Aim, design, and study setting

This is a multicentre, single-arm, open-label, phase II trial. All included patients will be treated with induction chemotherapy, consisting of FOLFOXIRI, prior to chemoradiotherapy. The study is registered in Clinicaltrials.gov (NCT04838496) and in the Netherlands Trial Register (NL9790), where a list of participating centres can be obtained. The primary aim of this study is to evaluate whether the addition of neoadjuvant chemotherapy with FOLFOXIRI prior to chemoradiotherapy results in a higher pCR rate or sustained clinical complete response (cCR) rate at 1 year in patients with hr-LARC, facing a particularly poor prognosis.

### Eligibility criteria

Patients, at least 18 years of age, with histopathologically confirmed, (deemed) resectable hr-LARC, with the low border of the tumour at or below the sigmoidal take-off as established on MRI, with a World Health Organization (WHO) performance status of ≤ 1, and fit for (modified dose) triplet chemotherapy are eligible for inclusion [59, 60]. An expected gross incomplete resection with overt tumour remaining in the patient after resection, tumour invasion in the neuroforamina, encasement of the ischiadic nerve and invasion of the cortex from S2 upwards are considered unresectable. Patients will be excluded in case of metastatic disease at inclusion, a homozygous DPD (dihydropyrimidine dehydrogenase) deficiency, any chemotherapy within the past 6 months, prior radiotherapy in the pelvic area interfering with the planned study treatment, any contraindication for the planned treatment, or concurrent malignancies that interfere with the planned study treatment or prognosis. Enlarged iliac or inguinal lymph nodes and aspecific lung nodules do not result in exclusion. All patients will be discussed during a multidisciplinary team (MDT) meeting to ensure their eligibility.

### Definition of hr-LARC

To ensure a study population with the most unfavourable prognosis in terms of disease-free survival, the definition of hr-LARC is based on the previously described, imaging-based characteristics that represent LARC at particularly high risk of treatment failure. Hr-LARC is therefore defined as LARC with on baseline MRI at least one of the following characteristics; indisputable tumour invasion into the MRF, EMVI grade 4, bilateral LLN with a SA of ≥ 7 mm, or extensive LLN involving pelvic side wall structures such as vessels, nerves or the ureter, at high risk of treatment failure, or tumour deposits. The presence of an “involved” or “threatened” MRF, or EMVI grade 3 is insufficient for inclusion in this study [55]. Moreover, consensus should be reached about the eligibility during a MDT meeting. A syllabus containing information and images of eligible hr-LARC will be provided to all participating hospitals.

### Interventions

Figure 1 provides a general flowchart of the study.

**Fig. 1 Fig1:**
[figure not shown]
Study flow diagram

#### Neoadjuvant chemotherapy

All included patients will receive neoadjuvant (induction) chemotherapy within 4 weeks after inclusion. Neoadjuvant chemotherapy consists of six two-weekly cycles of FOLFOXIRI (irinotecan 165 mg/m^2^ Body Surface Area (BSA), oxaliplatin 85/m^2^ BSA, leucovorin 400 mg/m^2^ BSA, 5-flourouracil 3200 mg/m^2^ BSA). Dose reductions are permitted on discretion of the medical oncologist.

Restaging will be performed with a pelvic MRI and a thoraco-abdominal computed tomography (CT) scan after four cycles of FOLFOXIRI. The timing of restaging should not interfere with the potential continuation of neoadjuvant chemotherapy. Radiological evaluation will be performed by a radiologist with expertise in abdominal imaging conform a standard operating procedure. The results will be discussed during a MDT meeting in one of the participating centres in the attendance of at least a surgical oncologist, a medical oncologist, a radiation oncologist, and a radiologist with expertise in abdominal imaging. If a patient has stable or responsive disease, neoadjuvant chemotherapy will be continued with two additional cycles of FOLFOXIRI. Subsequently, chemoradiotherapy will start within 3–6 weeks after the last cycle of neoadjuvant chemotherapy. If progressive, but still resectable disease is assumed during restaging, no further systemic therapy will be administered, and the patient will start with chemoradiotherapy within 3–6 weeks. If restaging suggests progressive, unresectable disease or the presence of distant metastases, the best palliative treatment will be offered according to standard of care.

#### Chemoradiotherapy

After neoadjuvant chemotherapy, all patients with (deemed) resectable disease will receive concomitant chemoradiotherapy according to standard of care within 3–6 weeks after the first day of the last cycle of FOLFOXIRI. Chemoradiotherapy will consist of 50 Gy or 50.4 Gy delivered in 25 or 28 fractions, respectively, with concomitant capecitabine (825 mg/m2 BSA) twice daily on radiotherapy days.

#### Treatment evaluation

Six to eight weeks after the last day of the chemoradiotherapy, restaging will be performed with a pelvic MRI and a thoraco-abdominal CT scan. The results will be discussed during a MDT meeting. A surgical resection will be planned for all patients with resectable disease after neoadjuvant treatment. In case of a cCR, a W&W strategy with close surveillance may be discussed with the patient by the treating physician according to standard of care. The presence of distant metastases or unresectable local disease will result in the best palliative treatment according to standard of care.

#### Surgery

Surgery will be performed according to the standard of care by a surgical team with experience in rectal cancer surgery, 10–14 weeks after the completion of chemoradiotherapy. The type and extent of the surgery and the possible addition of intraoperative radiotherapy (IORT) will be left to the discretion of the surgeon.

#### Follow-up

Patients’ follow-up will be performed according to standard of care every 3 months in the first 3 years and every 6 months thereafter up to 5 years postoperatively [1]. The level of carcinoembryonic antigen (CEA) will be determined at every follow-up moment. If during the follow-up the CEA level increases, a thoraco-abdominal CT scan will be performed according to the Dutch guidelines. At 6, 12, 18, 24, 30, 36, 48- and 60-months post-operatively, a thoraco-abdominal CT scan will be performed. A FDG-PET/CT scan is allowed, but not mandatory. In case of a W&W approach, the aforementioned follow-up will be expanded according to Dutch standard of care [23].

#### Questionnaires

All patients participating in the study will receive validated quality of life questionnaires after informed consent. Patients will be asked to complete the EORTC QLQ-C30, QLQ-CR29 (from the European Organisation for Research and Treatment of Cancer Quality of Life Group), and EQ-5D-5L (from the EuroQoL Group, Rotterdam, the Netherlands) at inclusion, 3, and 12 months post-operatively [61–63]. Patients receive questionnaires either by email or on paper, according to their own preferences.

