### Statistical methods

Demographics, patient, and tumour characteristics will be presented for all patients. Continuous data will be reported as mean with a standard deviation or as median with an interquartile range or 95% confidence interval, depending on the distribution. Categorical data will be reported as count, including a percentage. All statistical tests will be two-sided and a P-value of less than 0.05 will be considered as statistically significant.

The proportion of patients with a CR, defined as a pCR or a sustained cCR, will be compared to the CR rate of a comparable group of patients treated with chemoradiotherapy alone before surgery, as described in the available literature (i.e. 10%), performing a chi-squared goodness-of-fit-test.

The Kaplan–Meier method will be used to display survival curves. In addition, Hazard Ratio’s will be calculated using the Cox proportional hazard regression model and will be accompanied by 95% confidence intervals. Perioperative morbidity, surgical characteristics, and histopathological findings will be presented for all patients treated with a surgical resection. The incidence of toxicity related to neoadjuvant treatment will be presented separately for neoadjuvant chemotherapy and chemoradiotherapy. Health-related quality of life is graphically presented across all time points. Moreover, quality of life will be compared during those different time points using the ‘repeated measures ANOVA’. Incremental costs are calculated for the extra costs per additional patient alive and the extra costs per additional quality adjusted life year, respectively. The 95% confidence intervals for (differences in) costs and health outcomes will be generated by non-parametric bootstrapping, drawing samples of the same size as the original samples.

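### Every quality-of-life and EQ-5D assessment after baseline is timed from surgery, so patients without an operation have no defined assessment time and nobody has one between inclusion and 3 months after surgery

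*Protocol article*

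**What the plan says.** The Questionnaires section is inclusive about who is measured: "All patients participating in the study will receive validated quality of life questionnaires after informed consent". It fixes the times as "at inclusion, 3, and 12 months post-operatively" and gives no others.

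The same article describes three routes on which a patient may have no operation:

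- **Watch and wait.** Under Treatment evaluation: "In case of a cCR, a W&W strategy with close surveillance may be discussed with the patient".
- **Palliative treatment after chemoradiotherapy.** Also under Treatment evaluation: "The presence of distant metastases or unresectable local disease will result in the best palliative treatment according to standard of care".
- **Palliative treatment after the first restaging.** Under Neoadjuvant chemotherapy: "If restaging suggests progressive, unresectable disease or the presence of distant metastases, the best palliative treatment will be offered".

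The Follow-up section says of watch and wait: "In case of a W&W approach, the aforementioned follow-up will be expanded according to Dutch standard of care". It does not mention questionnaires. The Outcomes section gives patients with a clinical complete response a substitute starting date, the second restaging MRI, but only for disease-free survival.

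Quality of life and costs are secondary objectives. Under Statistical methods, "Health-related quality of life is graphically presented across all time points". The time points are then compared by repeated measures ANOVA, and an incremental cost per QALY is calculated.

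**The concern.** The schedule cannot be applied to everyone it is promised to. The patients for whom it is undefined are picked out by how treatment went: those who responded so well that surgery was deferred, and those whose disease became unresectable or metastatic. The first group can count as responders on the primary endpoint. If sites follow the schedule literally, the data after baseline come from a group selected by outcome. Conventional repeated measures ANOVA makes this worse, because it drops anyone without all time points.

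The second part concerns QALYs. With one EQ-5D before treatment and the next 3 months after surgery, utility over the whole of FOLFOXIRI, chemoradiotherapy, the wait and the operation has to be interpolated between two values that both lie outside that period. The burden of the intensified regimen, which the Discussion itself raises, would not enter the QALY. A later analysis plan cannot recover a questionnaire that was never sent.

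**Working it through.** **Plan's own figures.** The article states none for quality of life or QALYs. The only one used here is the total of 128, which follows from 121 evaluable patients and 5% drop-out: 121 / 0.95 = 127.4, rounded up to 128. It is used only as a denominator.

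**When the first questionnaire after baseline falls.** Inputs, in weeks:

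| Step | Section | Earliest | Latest |
|---|---|---|---|
| Inclusion to start of chemotherapy | Neoadjuvant chemotherapy | 0 | 4 |
| Start to day 1 of cycle 6 (5 × 2 weeks) | Neoadjuvant chemotherapy | 10 | 10 |
| Day 1 of last cycle to chemoradiotherapy | Chemoradiotherapy | 3 | 6 |
| Chemoradiotherapy, 25 or 28 fractions at 5 per week (assumed) | Chemoradiotherapy | 5 | 5.6 |
| End of chemoradiotherapy to surgery | Surgery | 10 | 14 |
| **Inclusion to surgery** | sum | **28** | **39.6** |

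- First questionnaire, 3 months (13 weeks) after surgery: 28 + 13 = 41 to 39.6 + 13 = 52.6 weeks after inclusion.
- Second questionnaire, 12 months (52 weeks) after surgery: 28 + 52 = 80 to 39.6 + 52 = 91.6 weeks.
- Counted from day 1 of cycle 6, the first falls at 3 + 5 + 10 + 13 = 31 to 6 + 5.6 + 14 + 13 = 38.6 weeks.

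So the interval without any EQ-5D covers from 41/52 = 79% of the first year to all of it. This assumes six cycles on schedule; a patient moved to chemoradiotherapy after the first restaging would reach surgery sooner.

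**What the existing restagings would offer.** The first follows four two-week cycles: 0 + 8 = 8 to 4 + 8 = 12 weeks after inclusion. The second is 6 to 8 weeks after chemoradiotherapy: 0 + 10 + 3 + 5 + 6 = 24 to 4 + 10 + 6 + 5.6 + 8 = 33.6 weeks. Both lie inside the unmeasured interval.

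**How many patients have no defined time.** The documents do not say. The one related figure is in the Discussion: 92% of the experimental arm of the cited triplet trial proceeded to surgery, so 8% did not. 0.08 × 128 = 10.2, about 10 patients. The watch-and-wait share is not given. If the total share without an operation were anywhere from 5% to 20% (an assumption), the count would be 0.05 × 128 = 6.4 to 0.20 × 128 = 25.6, about 6 to 26 patients.

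**Is an origin given anywhere else?** No. Disease-free survival has one for clinical complete responders, and the interim analysis trigger under Data monitoring counts surgery or entry into watch and wait. Neither is tied to the questionnaires, and neither covers patients who go to palliative treatment.

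**The case against.** Much of the other side is fair.

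- **All patients are named as recipients.** A reader might infer that watch-and-wait and never-operated patients will have no follow-up questionnaire at all. The article does not say so. What is established is an undefined time, not an exclusion.
- **The article uses post-operative wording loosely.** Follow-up counts visits and scans from surgery and then extends that follow-up to watch and wait. Translational research asks all patients for samples timed around surgery. This suggests the authors may intend questionnaires for everyone, but it supplies no date from which to count.
- **It is a journal article.** The full protocol, which is not shown, may set the origin. That is possible. However, the article states the questionnaire schedule as a specific list and, elsewhere, does deal explicitly with patients who are not operated.
- **Treatment burden is recorded.** A reader might infer that nothing is measured during or after FOLFOXIRI. That is not supported: in operated patients both later questionnaires come after it, and CTCAE toxicity is reported separately for chemotherapy and chemoradiotherapy. What stands is narrower: no questionnaire falls between inclusion and 3 months after surgery, and CTCAE grades give no utility value.
- **On-treatment questionnaires are a design choice.** True, and their absence contradicts nothing. It becomes a weakness because cost per QALY is planned.
- **The number affected.** It is tempting to add an assumed 5 to 20% in watch and wait to the 8% and report 13 to 28%, or 17 to 36 of 128. The documents do not support that sum. The first part is assumed. The second comes from a trial in which, by the article's own account, the worst-prognosis patients were underrepresented. The two may overlap, and some watch-and-wait patients may be operated on later.

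**Conclusion.** The point holds in limited form. The schedule gives no assessment time after baseline to patients without surgery, and in operated patients the first questionnaire after baseline falls about 41 to 53 weeks after inclusion. The timing rests on the stated intervals, six cycles on schedule and five fractions a week. The number of patients concerned is unknown; about 10 of 128 is an illustration from another trial, not an estimate for this one.

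Followed as written, the schedule leaves the ANOVA and the cost per QALY resting on patients selected by treatment outcome, with utility over the neoadjuvant period purely interpolated. Whether sites will follow it that literally cannot be settled from the article. The primary endpoint and its sample size are untouched. It is worth changing because the change is cheap while patients are still being followed and cannot be made afterwards.

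**What to change.** 1. **Define the origin.** Give patients without surgery a questionnaire origin so that all patients are assessed at comparable times. One option is a common origin for everyone, at inclusion or at the end of chemoradiotherapy. From the end of chemoradiotherapy, the current times correspond to 10 + 13 = 23 to 14 + 13 = 27 weeks and 10 + 52 = 62 to 14 + 52 = 66 weeks. The other option is to keep surgery as origin for operated patients and use the second restaging MRI for clinical complete responders, as disease-free survival already does. Planned surgery falls 10 − 8 = 2 to 14 − 6 = 8 weeks after that MRI, so the times would stay close. Patients who progress earlier need inclusion as their origin, since the later dates may not exist for them.
2. **Add the two existing restagings.** Send the same questionnaires after cycle 4 and at the restaging 6 to 8 weeks after chemoradiotherapy, so that QALYs over the neoadjuvant period rest on measured values.
3. **Change the analysis.** Use a method that keeps patients with incomplete time points, such as a mixed model. This complements step 1 and does not replace it: a patient with only a baseline value still says little about later quality of life.
4. **If this is not adopted,** state that quality-of-life and QALY results apply to operated patients only, and say how utility is valued between inclusion and the first post-operative EQ-5D.

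The cost is a small amendment and two more mailings per patient, by the email or paper route already in use. The downsides are a slight added burden for patients and a mixed schedule, since those already enrolled would join at their next time point.
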